## 2. Methods

### 2.1. Study Design

In accordance with the Consolidated Standards of Reporting Trials statement (CONSORT) [27,28], a pilot, cluster-randomized controlled trial (RCT) will be conducted. Due to the nature of the intervention, a double-blind study design is not possible given that participants will be aware of their group designation, and as such, a single-blind design will be adopted (all assessments will be conducted by research staff who remain unaware of group assignment). This study received ethical approval from the University of Western Ontario’s Research Ethics Board (REB# 111890) and is registered with the Clinical Trials Registry provided by the US National Library of Medicine (NCT03695523; https://clinicaltrials.gov/).

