### 2.4. Recruitment and Randomization

To secure an adequate sample size, this study will be conducted in eight randomly selected childcare centres (i.e., the clusters) chosen from an online listing of 55 eligible licensed childcare centres in London, Canada. Since it is necessary to implement the policy at the centre-level to groups of children, the childcare centres (i.e., the clusters) rather than the individual participants, will be randomly allocated by the project coordinator to either implement the physical activity policy (experimental; *n* = 4), or maintain their daily programming (control; *n* = 4) for the eight-week intervention period (at which time the policy will no longer be enforced).

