### 2.5. Participants

The project coordinator will invite all toddlers (18 months–2.4 years) and preschoolers (2.5 years–4 years) to participate, and those whose parents/guardians provide written consent will be eligible to participate in the study. Childcare providers and directors from randomly selected childcare centres will also be invited to participate. Participants will receive a small token of appreciation as thanks for their time. See Table 1 for complete inclusion/exclusion criteria for the Childcare PLAY Policy study.

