### 2.6. Development and Implementation of the Childcare PLAY Policy

To promote policy engagement, buy-in, and suitability, the policy was developed by our research team in collaboration with an advisory committee that included childcare organizations and centre administrators, childcare providers, municipal childcare stakeholders, and a policy expert. The policy was created following a review of relevant literature on the importance of outdoor play [32], unstructured activity [29,33], and informed by the Canadian 24-Hour Movement Guidelines for the Early Years (0–4 years; [3]). The current version of the policy includes eight statements that are designed to provide specific recommendations for time in energetic play (i.e., minimum of 40 min/day), outdoor time (i.e., 120 min/day), and suggests short (i.e., 15–30 min), frequent (i.e., 3–4 times/day) outdoor periods during childcare hours. It requires that children be exposed to a variety of indoor and outdoor physical activities to promote physical literacy and recommends appropriate role modelling of screen-based technology, with no screen time permitted for children during childcare hours. Sustained sedentary time is recommended to be disrupted and replaced with physical activity. See Appendix A for the Childcare PLAY policy.

Experimental Condition. For eight weeks, childcare providers in the experimental centres will be asked to implement the written policy that outlines optimal physical activity daily affordances and sedentary time recommendations during childcare. Prior to the eight-week intervention period, childcare providers will participate in a training session, led by the project coordinator. The session will last approximately an hour in length, which will detail the characteristics of the study design, review the policy, its implementation, and study tools (e.g., accelerometer logs).

Control Condition. Childcare centres randomly assigned to the control group will be asked to continue their typical daily curriculum for the duration of the eight-week intervention and follow-up period. Upon completion of the study, all centres allocated to this group may opt to receive a copy of the written physical activity policy and the training regarding its implementation.

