### 2.7. Measures

A variety of tools will be used to assess the feasibility and effectiveness of the Childcare PLAY Policy (Table 2).

Demographic Information (Parents and Childcare Providers). Parents of participants will be asked to complete a demographic questionnaire at baseline to describe participants and their families (e.g., children’s age, sex, ethnicity, family income, parental education), as well as the children’s physical activity participation outside of childcare (e.g., organized sport or activities). Parental/guardian weekly engagement in MVPA and their view of themselves as a physical activity role model will be measured. Childcare providers and directors will complete a demographic questionnaire at baseline to capture information related to their age, sex, employment status, years of childcare experience, and level of education. Childcare providers will also report time in MVPA and their view of themselves as physical activity role models. No personal identifiers will be stored with participant data.

Physical Activity (Children). Toddlers’ and preschoolers’ physical activity will be measured using ActiGraph™ (ActiGraph, LLC, Pensacola, Florida) accelerometers—the gold standard for measuring young children’s sporadic physical activity patterns in field settings [34,35,36]—for five consecutive days, during childcare hours only. This process will be undertaken pre-intervention (week 0), mid-intervention (week 4), post-intervention (week 9), and at six-month follow-up. Raw data will be collected to capture the sporadic activity and intermittent periods of rest of the young participants. The accelerometers will be worn on the right hip (above the iliac crest) and will begin collecting activity data on the morning of the first day of data collection. Wear-time of the accelerometers (i.e., the time when it is fitted and removed from each child) will be recorded for each participating child by childcare providers using a daily log. Validated and age appropriate cut-points will be applied to the data to delineate the different activity intensities [37].

Anthropometric Measures (Children). Height (using a Seca 214 “Road Rod” Portable Stadiometer; nearest 0.1 cm), weight (using a Tanita 700-TBF300GS Body Fat Analyzer w/Goal Setter scale; nearest 0.1 kg), and waist circumference (using a measuring tape; nearest 0.1 cm) will be assessed at baseline. The data collected will be used to calculate the child’s standardized body mass index score (BMI-z).

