Childcare Environment (Childcare Providers and Directors). The validated Environment and Policy Assessment and Observation—Self-Report (EPAO-SR; [39]) instrument examines the classroom physical environment and physical activity practices in childcare centres; this tool consists of two subscales, Space, Equipment, and Environment (eight items) and Practices around Physical Activity (three items). We will adapt the tool to conform with the Canadian context and remove the nutrition content (as seen in Ott et al.’s paper) [22]. This tool will be administered to childcare providers once during each week of data collection. The information solicited from this questionnaire will provide useful context to help better understand each classroom’s physical activity environment and practices and whether these change after the policy is implemented. The EPAO-SR Today [39], which entails six subscales (Morning Outdoor Activities (seven items); Morning Indoor Activities (eight items); Nap/Rest Time (three items); Afternoon Outdoor Activities (seven items); Afternoon Indoor Activities (three items); and Other Activities (three items)) will also be completed by one childcare provider per classroom on one chosen day at each data collection time point. This validated tool provides a snapshot of the specific activities in which the children engaged during morning and afternoon indoor and outdoor periods. Finally, the validated Director General EPAO-SR [39], which consists of two subscales (Childcare Environment (six items) and Physical Activity Policies (11 items)) also adapted for use in Canada without the nutrition subscale, will be administered to all centre directors at baseline. This will assess the presence of any existing physical environment characteristics that may inhibit or promote physical activity, and existing policies related to physical activity and sedentary time that may exclude a centre from participating in the study.

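### The statement that blinded research staff make all assessments is wrong as written: six of the seven instruments used after baseline come from providers who know their arm

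*Protocol article*

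**What the plan says.** Section 2.1 rules out double-blinding, "given that participants will be aware of their group designation", and adopts a single-blind design in which "all assessments will be conducted by research staff who remain unaware of group assignment".

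Other sections describe who does what:

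- Section 2.4: the centres "will be randomly allocated by the project coordinator to either implement the physical activity policy" or to carry on as usual.
- Section 2.5: "The project coordinator will invite all toddlers" and preschoolers. Providers and directors are also enrolled as participants.
- Section 2.6, under the experimental condition: before the intervention period, "childcare providers will participate in a training session, led by the project coordinator". The session covers the policy and also study tools, with accelerometer logs as the example. The control paragraph mentions training only after the study ends.
- Section 2.7: accelerometer wear-time "will be recorded for each participating child by childcare providers using a daily log". The same section has providers complete the adherence log, the self-efficacy questionnaire, the program evaluation survey and both provider versions of the EPAO-SR, and places the interviews in the experimental arm.

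**The concern.** The blinding sentence makes a claim about every assessment, but the measures section gives most of them to people who are not research staff and who know their arm. A reader who trusts section 2.1 would take changes in self-efficacy and in the childcare environment as blinded findings. They are reports by providers who, in one arm, have been trained in the policy and asked to change the practices they report on. Such reports can shift without any change in practice.

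The second strand is recruitment. In a cluster trial, selection bias can enter when children are invited by someone who already knows which arm their centre is in. Here one role both allocates and invites, and the article does not say which comes first.

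**Working it through.** The plan gives no figure to reproduce on this point. The check is a count from Table 2, followed by a comparison of sections.

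**1. Instruments used after baseline.** Table 2 has 11 rows. Four are baseline-only: the parent and provider demographic questionnaires, anthropometrics and the Director General EPAO-SR. That leaves 11 − 4 = 7.

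**2. Source of each (section 2.7 and Table 2).**

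| Instrument | Source | Can the source be unaware of arm? |
|---|---|---|
| Policy adherence log | Provider | No |
| Self-efficacy questionnaire | Provider | No |
| Program evaluation survey | Provider, experimental arm only | No |
| EPAO-SR General | Provider | No |
| EPAO-SR Today | One provider per classroom | No |
| Interview | Provider, experimental arm only | No, and neither can the interviewer |
| ActiGraph accelerometry | Device | Activity signal yes; wear-time log no |

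Provider-completed: 5 of 7. Provider-sourced once the interview is added: 5 + 1 = 6 of 7. The remaining one is a device measure with a provider-kept log.

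**3. Which objectives this reaches.** Section 1 defines feasibility by whether the policy was delivered as planned and liked by providers, and the abstract says it will be assessed through staff surveys and interviews. The primary aim therefore rests on provider-sourced data. So do objective (iv), self-efficacy, and objective (v), environmental change. Objectives (i) and (ii), on physical activity and sedentary time, rest on the device. Lack of blinding reaches them less directly, through the wear-time log and through provider behaviour in measurement weeks.

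**4. Allocation and recruitment.** Sections 2.4, 2.5 and 2.6 give allocation, invitation of children and provider training to the same coordinator. No section says whether children are invited before or after centres are allocated. Table 1 requires at least eight consented children for a centre to be included, which hints that some consent comes first. It does not establish that all consent does.

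**5. Instruction in the wear-time log.** Providers need the log at week 0, when accelerometry starts in both arms. The only session described as covering it appears under the experimental condition. A briefing for control centres may exist but is not stated.

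**The case against.** The best defence is that much of this is disclosed. The sentence that claims blinded assessors also says that participants know their group, the EPAO-SR carries self-report in its name, and section 2.7 says that providers rate their own confidence. The survey and interviews have no control arm. Section 2.8 treats the adherence log and self-efficacy change descriptively. Assessor blinding matters most where arms are formally compared, and the leading comparisons, TPA, MVPA and sedentary time, are device-measured. This limits the consequences, but it does not make the statement true. EPAO-SR is both provider-reported and modelled by group and time in section 2.8.

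Three stronger readings are tempting, and the article does not support them.

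- *The coordinator's roles contradict assessor blinding.* A reader might infer this, but the article never says that the coordinator assesses anyone. Allocating, inviting and training are compatible with separate blinded assessors.
- *Recruitment bias is present.* The order of consent and allocation is unstated, and a condensed article may leave it to the full protocol. All toddlers and preschoolers are to be invited, which limits selection by the recruiter, though not by parents.
- *Centres could be lost after allocation.* The baseline director survey looks for "existing policies related to physical activity and sedentary time that may exclude a centre from participating in the study", so a reader might picture an allocated centre being removed. But a baseline survey need not follow allocation, section 2.4 draws from a list of eligible centres, and no section describes such a removal.

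**Conclusion.** The blinding statement in section 2.1 is wrong as written and should be narrowed. Of the seven instruments used after baseline, five are completed by providers who know their arm, a sixth is an interview whose conductor must know the arm, and the seventh depends on a provider-kept wear log. The count rests on Table 2 and on section 2.1's own statement that participants know their group.

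The effect on device-measured activity is indirect. Its size cannot be worked out, because the article does not say how the wear log enters the derived outcomes.

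On recruitment, the conclusion is weaker: one role holds the allocation and issues the invitations, so bias is possible but not shown, and its size cannot be computed. A guard is still worth adding because it is cheap and because this pilot is meant to inform a larger evaluation.

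**What to change.** 1. **Blinding wording.** Restate section 2.1 so that blinding covers only the staff who fit monitors, take anthropometry and process accelerometer files. The article does not say who fits the monitors each day. If providers do, leave that task out of the statement.
2. **Labelling.** Report and interpret EPAO-SR, self-efficacy, adherence-log and survey results as unblinded self-report. State that the interviews were held with the arm known.
3. **Order and allocation.** Complete director screening, parental consent and week-0 measures in all eight centres, then have the allocation generated by a team member without centre contact. If this order was already followed, one sentence saying so is enough. Parts of the article are in the past tense, so conduct may have begun. If the order was different, report the order used.
4. **Training.** Give accelerometer-log instruction to both arms before week 0, and hold only the policy training until after allocation.

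Items 1 and 2 cost only wording. Items 3 and 4 mean that the training session is split and its policy part comes later. Delaying the whole session would not work, because providers need the log instruction at week 0.

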### 2.2. Ethics Approval and Consent to Participate

Ethical approval was provided by the Health Sciences Research Ethics Board at The University of Western Ontario (REB# 111890). Parents/guardians of participating children provided written consent, and children offered assent when the accelerometer was placed on them. Childcare providers also provided written consent prior to participation.

### 2.3. Sample Size

To secure a representative sample of children in childcare, a random cluster sampling strategy will be used. In a meta-analysis exploring the effectiveness of 15 physical activity interventions targeting preschool-age children, Gordon and colleagues [29] reported that most studies had a small-to-moderate effect (Hedges *g* = 0.4) for change in young children’s total physical activity levels after participating in an intervention. If we convert this to f2, we can estimate this effect size to be approximately 0.12. Using the pwr package [30] within R version 3.6.0 [31], a minimum sample size of 99 children will be required (assuming 80% power and an experiment-wise alpha of 0.05). To account for a clustering effect, using an intra-cluster coefficient of 0.05, and an average cluster size of 16 children, the design effect is: 1 + 0.05 (16 − 1) = 1.75. Therefore, the sample size will be inflated to 175. Based on our recently conducted studies using accelerometry within the childcare environment [9], an anticipated loss to follow-up/accelerometer non-compliance rate of 20% is anticipated. To adjust for this, we aim to recruit 218 children.

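### Section 2.3 converts Hedges g = 0.4 to f² of about 0.12; for two equal groups it is 0.04, so 80% power at 0.4 SD is not supported

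*Protocol article*

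**What the plan says.** Section 2.3 takes its planning effect from a meta-analysis of physical activity interventions in preschool-age children, which "reported that most studies had a small-to-moderate effect (Hedges *g* = 0.4) for change in young children’s total physical activity levels". It continues: "If we convert this to f2, we can estimate this effect size to be approximately 0.12". From that value, using the R package pwr, it concludes that "a minimum sample size of 99 children will be required (assuming 80% power and an experiment-wise alpha of 0.05").

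Two inflations follow. For clustering, "the design effect is: 1 + 0.05 (16 − 1) = 1.75", and "Therefore, the sample size will be inflated to 175". For missing data, "an anticipated loss to follow-up/accelerometer non-compliance rate of 20% is anticipated", and "To adjust for this, we aim to recruit 218 children".

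The section gives no conversion formula, no numerator degrees of freedom for the power routine, and no correlation between repeated measurements. Section 2.4 fixes the design at eight centres, four per arm.

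**The concern.** Converting a two-group standardised difference to Cohen's f² is a fixed identity, and 0.12 is not what it gives for 0.4. The step from 0.4 to 0.12 triples the effect size on the f² scale, and every later number in the section (99, 175, 218) depends on it.

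At stake is the only power claim in the article. As written, it says the trial has 80% power for an effect of the size seen in earlier interventions. If the planning effect really is 0.4 SD, the chance of detecting it is much lower, and a non-significant result on children's activity would say less than the claim implies. The Background section presents this pilot as a step towards a larger effectiveness study, so the same conversion could be carried into that study's sample size.

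**Working it through.** **Inputs** (all from section 2.3 unless noted): g = 0.4; stated f² = 0.12; power 80%; alpha 0.05, taken as two-sided; stated n = 99; design effect 1.75 (ICC 0.05, cluster size 16); loss 20%; eight centres, 4 v 4 (section 2.4).

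**1. Reproducing the stated figures.** The f² routine in pwr uses a noncentral F with λ = f²(u + v + 1). Solving at f² = 0.12, alpha 0.05 and power 0.80:

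| u | v | N = u + v + 1 |
|---|---|---|
| 1 | 65.4 | 67.4 |
| 2 | 80.4 | 83.4 |
| 3 | 90.9 | 94.9 |
| 4 | 99.3 | 104.3 |

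So 99 can be recovered as v at u = 4. It can also be recovered as N at u = 3 if the unrounded f² was 0.115 (N = 98.8). It also equals the per-arm size of a two-sided two-sample t-test at d = 0.4 (99.08 per arm). The article does not say which applies.

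The inflations are close to what is stated: 99 × 1.75 = 173.25 (175 is 100 × 1.75), and 175/0.8 = 218.75.

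**2. The conversion.** For two equal groups f = d/2, so f² = d²/4 = 0.16/4 = 0.04. Through the correlation: r = 0.4/√(0.16 + 4) = 0.196, and r²/(1 − r²) = 0.04. Neither r² (0.038) nor d² (0.16) gives 0.12. In reverse, f² = 0.12 corresponds to d = 2√0.12 = 0.69.

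**3. Could a correlation explain it?** If variance explained by baseline or repeated measures were credited, f² becomes 0.04/(1 − r²). Setting this to 0.12 gives 1 − r² = 1/3, so r = 0.82. The section states no such value and describes the step as a conversion of g.

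**4. Children needed at f² = 0.04**, 80% power, before clustering:

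- 1-df two-arm comparison: about 198, or 200 with whole numbers per arm by t-test.
- u = 3: 277. u = 4: about 304.

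For the 1-df comparison with the section's own inflations: 198 × 1.75 = 346.5 and 200 × 1.75 = 350 analysed; 347/0.8 = 434 and 350/0.8 = 438 recruited, rounded up.

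**5. Power of the stated 99 at 0.4 SD.** 1 df: 50%. u = 3: 34%. u = 4: 30%.

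**6. Power of the fixed design at 0.4 SD, 175 analysed:**

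- Stated design effect: effective n = 175/1.75 = 100. Unadjusted power is 51% (t-test with child-level df).
- Actual cluster size: 175/8 = 21.9 per centre. Design effect 1 + 0.05 × 20.9 = 2.04; effective n = 85.6. Unadjusted power is 46% (normal approximation) or 34% (6 centre-level df).
- Same effective n with an assumed baseline correlation of 0.5: 57% (normal) or 44% (6 df). With 0.7: 74% or 58%.
- Stated design effect with correlation 0.7: 80% (normal).

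**The case against.** The strongest reply is that this is a pilot whose primary aim is feasibility. Child activity is a secondary objective, and a larger study is planned. That stands, and it is why no increase in size is asked for. It does not rescue the number: a pilot need not be powered, but a power claim that it makes should follow from its inputs.

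The second reply is that section 2.8 plans mixed models over four occasions including baseline, so an unadjusted comparison understates power. This also stands in part. With a baseline correlation of 0.7, the stated design effect and a normal approximation, power at 0.4 SD does reach 80%. But that assumption appears nowhere in section 2.3, and it would need to be stated and justified.

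A reader might also infer more than the text supports:

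- **That the design has 80% power at 0.69 SD exactly.** That figure only restates the f² input. In a 1-df comparison, 99 independent children reach 80% power at about 0.57 SD.
- **That 99 is a degrees-of-freedom value or a per-arm number mistaken for a total.** Three routes lead to 99, and the article does not allow a choice between them.
- **That eight centres can never reach the requirement**, because effective n is limited to 8/0.05 = 160. That comparison holds only without baseline adjustment. With a correlation of 0.5 the requirement falls to about 198 × 0.75 = 149, which is below 160.

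**Conclusion.** The conversion is wrong as written: g = 0.4 is f² = 0.04, and 0.12 is three times that. The claim of 80% power for the cited effect is therefore unsupported, and 99, 175 and 218 do not follow from g = 0.4. In a simple two-arm comparison the stated 99 is about half of what is needed.

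The conversion result assumes two equal groups. The sample sizes add two-sided alpha 0.05 and no credit for baseline correlation. The power of the fixed design depends on further assumptions: about 50% unadjusted with the stated design effect, about 34 to 46% with about 22 children per centre (the lower end on 6 centre-level df), and higher if baseline correlation is credited. Cluster size and the small number of centres are separate matters from the conversion, so no single replacement power figure should be given without its assumptions. The documents also do not say that a null result will be read as evidence against a 0.4 SD effect; that is a risk of the current wording, not a stated plan.

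**What to change.** In section 2.3:

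1. Replace f² = 0.12 with 0.04, or state and justify the correlation that produces 0.12.
2. Withdraw the claim of 80% power for g = 0.4.
3. State the test behind the calculation, including its numerator degrees of freedom, so that the figure can be reproduced.
4. Restate the power of the fixed design (eight centres, about 175 analysed) at 0.4 SD as a short range. Name for each figure the ICC, the children per centre, the degrees of freedom and any baseline correlation.
5. Say that the child activity results will be reported as estimates with 95% confidence intervals to inform the larger trial.

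This is a rewording. It needs no extra children or centres. The cost is a less favourable stated power.

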### 2.8. Analysis

All data will be entered, verified, and stored in our lab. Baseline characteristics of the children and the childcare centres will be summarized descriptively; participant characteristics for those who complete the study and those who drop out will be explored. All statistical analyses will be performed in R [31], using the lme4 [40] and lmerTest packages [41].

Implementation Log. Frequencies and percentage scores will be calculated to reflect adherence to policy statements and reasons that compliance was not attained will be reported descriptively.

Program Evaluation Survey and Interviews. Means and standard deviations of survey item ratings will be provided. Responses to open-ended program evaluation survey and interview questions will be analyzed using thematic content analysis [42] using QSR NVivo.

Physical Activity. Children’s physical activity data will be analyzed using a series of linear mixed effects models for each of the three outcome variables (i.e., TPA, MVPA, and sedentary time). Group (experimental versus control) and time (baseline, mid-intervention, post-intervention, and six-months post-intervention) will be modelled as a fixed effect, and will be evaluated using *t*-tests, with a Satterthwaite approximation determining degrees of freedom. Descriptive survey data will be analyzed using frequencies, *t*-tests, and chi-square tests.

Childcare Providers’ Self-Efficacy. Descriptive statistics will be reported to indicate changes in childcare providers’ self-efficacy specific to implementing physical activity in childcare. Classical test theory will be used to assess internal consistency of the scales, exploratory factor analysis will be used to assess the factorial validity of the measured constructs, and item response theory will be used to explore the item and scale characteristics of the measurements used to assess the two polytomous constructs in this study (i.e., task and barrier self-efficacy). Factor analysis and classical test theory analyses will be undertaken within the psych package [43] and the ltm package [44] will be used for the item response theory analyses.

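### The minimum of 99 children at 80% power does not follow from f2 = 0.12 and alpha 0.05 for the t-tests the analysis uses, and the test behind 99 is not stated

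*Protocol article*

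**What the plan says.** Section 2.3 (Sample Size) starts from a meta-analysis of preschool activity interventions with Hedges g = 0.4 for total physical activity. It then converts: "If we convert this to f2, we can estimate this effect size to be approximately 0.12". The software is given ("Using the pwr package [30] within R version 3.6.0 [31"), but not the function, the numerator degrees of freedom or the hypothesis tested. The result is "a minimum sample size of 99 children will be required (assuming 80% power and an experiment-wise alpha of 0.05".

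The chain continues with "the design effect is: 1 + 0.05 (16 − 1) = 1.75", then "Therefore, the sample size will be inflated to 175", and after a 20% allowance for loss and non-compliance, "To adjust for this, we aim to recruit 218 children".

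Section 2.8 (Analysis, Physical Activity) fits linear mixed models to TPA, MVPA and sedentary time with group and time as fixed effects. These are evaluated by t-tests, "with a Satterthwaite approximation determining degrees of freedom". No omnibus F-test is named for these outcomes, and no division of alpha is given.

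**The concern.** A t-test on a model coefficient has 1 numerator degree of freedom. A sample size derived from f2 depends strongly on that number, so 99 at 80% power can be checked against the test in section 2.8. It does not match. If 99 was derived for some other test, or at another alpha, or as a per-group count, then the printed 80% is not the power of the tests that will be reported. A reader faced with a null t-test on TPA could not tell whether the trial was well powered or had about an even chance of missing the assumed effect.

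**Working it through.** **Inputs (section 2.3):** g = 0.4; f2 = 0.12 (0.115 to 0.125 before rounding); power 0.80; alpha 0.05; design effect 1.75; loss 20%. **Input (section 2.8):** t-tests, so u = 1.

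**Formula.** For a test with u numerator and v residual df, N = u + v + 1 and the noncentrality is lambda = f2 x N. Solve for v so that the noncentral F gives 80% power, round v up, and add u + 1.

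**Step 1. The plan's figure on its own inputs (f2 = 0.12, alpha 0.05).**

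| u | v at 80% power | N | N for f2 0.125 to 0.115 | power at N = 99 |
|---|---|---|---|---|
| 1 | 65.38 | 68 | 65 to 71 | 92.7% |
| 2 | 80.36 | 84 | 81 to 87 | 86.9% |
| 3 | 90.85 | 95 | 92 to 99 | 81.9% |
| 4 | 99.32 | 105 | 101 to 109 | 77.5% |

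No row gives 99 at f2 = 0.12. For the 1-df test, no f2 that rounds to 0.12 brings the requirement near 99.

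**Step 2. Routes that do reach 99 or come close.** Each needs something the article does not state.

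- *3 df, f2 near 0.115:* v = 94.80, N = 99.
- *4 df, residual df read as N:* v = 99.32, while the N it implies is 105.
- *Experiment-wise alpha split across tests:* 1 df at 0.05/4 = 0.0125 gives N = 97 (93 to 101 over the rounding range of f2); 2 df at 0.025 gives N = 100. A split over the three outcomes (0.0167), with 1 df, gives 91 (87 to 94).
- *Two-sample t-test on g = 0.4, two-sided 0.05:* noncentrality g x sqrt(n/2) = 0.4 x sqrt(49.5) = 2.81 at n = 99 per group. Power is 0.7997 at 99 and 0.8036 at 100 per group, so the solution is just over 99 **per group**.

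**Step 3. What the last route would mean.** With 99 children in total (49.5 per group) the noncentrality is 0.4 x sqrt(24.75) = 1.99, and power is about 50%.

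**Step 4. The rest of the chain.**

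- Design effect: 1 + 0.05 x 15 = 1.75, as printed.
- Inflation: 99 x 1.75 = 173.25; 100 x 1.75 = 175. The printed 175 starts from 100.
- Loss: 175/0.8 = 218.75, printed as 218.
- Backwards from 218: 218 x 0.8 = 174.4, and 174.4/1.75 = 99.7 effective children. So the powers at 99 to 100 apply to the recruitment target under the plan's own design effect.

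**The case against.** A reader might infer that 99 must come from a 3- or 4-df omnibus test, so that the plan sized one test and decides by another, and that the two could give opposite conclusions. The documents do not support this. At f2 = 0.12 those tests need 95 and 105. They meet 99 only with f2 at the edge of its rounding range or with residual df mistaken for N. The step from 100 to 175 fits 99.3 rounded up, but it fits 99.08 per group rounded up equally well. No omnibus test is planned, so there is no second result for a t-test to contradict. For the same reason, carrying 105 through the chain to a larger recruitment target would rest on a guess.

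Against the narrower point, three things can be said.

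- **The error may be harmless.** If f2 = 0.12 is accepted, 99 children is more than a 1-df test needs, and 80% is an understatement. That is correct and limits the severity. It does not dispose of the point, because the route from g = 0.4 would leave about 50%. The usual two-group relation f2 = g²/4 = 0.04 leads to the same place: 199 children in total for a 1-df test. Whether g = 0.4 should become 0.12 is a separate question.
- **"Experiment-wise" may mean a smaller per-test alpha.** It may, and that could account for a figure near 99. But no split is given, and dividing by the three named outcomes gives 91.
- **This is a condensed article on a pilot whose primary aim is feasibility.** The numerator df alone could fairly be left to a fuller document. Here, however, the article prints a size, a power and a multiplication that do not agree with one another or with the test it names.

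**Conclusion.** The point holds in limited form. The stated 99 children and 80% power do not belong to the t-tests of section 2.8 at the stated f2 and alpha: those tests need 68 children and have about 93% power at 99. What produced 99 cannot be recovered from the article. Depending on the route, a 1-df test with 99 children before clustering has between about 50% and 93% power. Separately, 175 does not follow from 99.

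These figures take the plan's design effect as given and do not allow for the small number of centres (eight), which also limits the degrees of freedom for the group effect. They do not show which route was used, nor that the recruitment target is wrong. The correction should be made, but it is no obstacle to the trial.

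**What to change.** In section 2.3, name the test being sized, its numerator df, its per-test alpha, and whether the count is a total or per group. In section 2.8, make that same test the deciding one for TPA. One 1-df contrast would serve, such as the between-arm difference in change from baseline to one named intervention-period measurement. Then restate the minimum N, the inflated N and the power from a single unbroken chain.

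If f2 = 0.12, alpha 0.05 and a 1-df test are kept, the chain is 68, then 68 x 1.75 = 119, then 119/0.8 = 148.75, or 149 children; the 218 planned would give about 93% power. If the two-sample test at g = 0.4 was meant, the power to state for 218 is about 50%.

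The cost is one recalculation and a few sentences. No extra children are needed as long as 218 is kept and the power is stated as it then is.
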